**7.2****Observation/Examination Items and Schedule**

**7.2.1　Observation/Examination Schedule**

The survey, observation, and evaluation items, along with the visit schedule for this study, are as follows.

|  | Pre-regist.  ~ Regist. | Surg. Date | PO 1 w | Discharge date | PO 30 d | PO 1y | PO 2 y |  |
| --- | --- | --- | --- | --- | --- | --- | --- | --- |
| Allowed Period |  |  |  |  | Within  ±14d | Within  ±56 d | Within ±56d | |
| Registration/Assignment | ● |  |  |  |  |  |  |  |
| Patient Background Information | ●※1 |  |  |  |  |  |  |  |
| Surgery (Protocol Treatment) |  | ● |  |  |  |  |  | |
| Surgery Information |  | ● |  |  |  |  |  |  |
| Intraoperative Complications/Adverse Events |  | ● |  |  |  |  |  |  |
| Early Postoperative Complications/Adverse Events |  |  |  |  |  |  |  |  |
| Medical History/Physical Examination | ●※1 |  | ● | ● | ● | ● | ● |  |
| JOA score | ●※1 |  |  |  |  | ● | ● |  |
| Cervical Plain X-ray  (Cervical Alignment) | ●※1 |  | ● |  |  | ● | ● |  |
| Cervical Plain CT  (Postoperative: Enlarged Laminar Retention Rate, Hinge Fracture/Bone Union) | ●※1 |  | ● |  |  | ● | ● |  |
| Cervical Plain MRI  (Paraspinal Muscle Cross-sectional Area) | ●※1 |  |  |  |  | ● | ● |  |
| Cervical Plain MRI  (Dural sac Area) | ●※1 |  |  |  |  | ● | ● |  |
| Cervical Plain MRI  (Grading of the mass posterior to the dural sac) |  |  |  |  |  | ● | ● |  |
| Late Postoperative Complications/Adverse Events |  |  |  |  |  |  |  |  |
| Health-Related QoL（EQ-5D） | ●※1 |  |  |  |  | ● | ● |  |
| Pain/Numbness Severity (VAS) | ●※1 |  |  |  |  | ● | ● |  |
| Cervical Disability Index (NDI) | ●※1 |  |  |  |  | ● | ● |  |
| Outcome Follow-up |  |  |  |  |  | ● | ● |  |
| Direct Medical Costs |  |  |  |  |  |  |  |  |

● ：Required

※1 : All surveys, observations, and tests related to this clinical study will be conducted after obtaining written consent from the research subjects. However, results from surveys, observations, tests, etc., performed as part of routine care prior to obtaining consent may be used as research data if they were conducted within 360 days prior to registration.

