The retention rate is calculated for each enlarged lamina identified on CT scans at postoperative 1 and 2 years, following previous reports^7)^ (Figure 4). The mean retention rate is also calculated for each patient.

(8) Proportion of hinge fractures at postoperative 1 and 2 years

(9) Percentage of bone union of gutter at postoperative 1 and 2 years

[Definition]

Using CT images at 1 and 2 years postoperatively, evaluate the presence or absence of hinge fractures (fractures of the groove created in the medial facet joint) and bone union in each enlarged lamina, following previous reports^8)^. Evaluate both on horizontal slices. A fracture is defined as a complete disruption of the cortical bone continuity of the target lamina. and bone union is defined as the formation of even partial bony continuity within the excavated groove region of the target lamina. The level and lateral side of each lamina are recorded.

[figure not shown]
(10) Sagittal alignment of cervical spine at postoperative 1 and 2 years (C-SVA, C2-7 angle, T1 slope)

[Definition]

Cervical spine alignment (C-SVA, C2-7 angle, C7 slope) is measured from plain radiographs at postoperative 1 and 2 years, according to previous reports^7)^ (Figure 5). Note that the C2-7 angle is denoted with a positive (+) sign for lordosis.

(11) Paraspinal muscle cross-sectional area (C4/5 level) at postoperative 1 and 2 years

[figure not shown]
[Definition]

Measure the cross-sectional area of paraspinal muscles (mm^2^) on the C4/5 slice of T2-weighted images according to a previous report^20)^, and calculate the total values for each side (Figure 6).

(a: multifidus, b: cervical semispinalis, c: cervical splenius capitis, d: splenius capitis)

(12) Dural sac cross-sectional area (C3/4, C4/5, C5/6, C6/7 levels) at postoperative 1 and 2 years

[Definition]

Measure the dural canal cross-sectional area (mm^2^) on the T2-weighted horizontal slice at each of the C3/4, C4/5, C5/6, and C6/7 levels, following the method described in a previous report^21)^ (Figure 7).

(13) Grading of the mass posterior to the dural sac at postoperative 1 and 2 years

［Definition］

The classification of posterior dural canal compression on the central slice of the T2 sagittal image is evaluated according to a previous report^22)^ (Figure 7).

[figure not shown]

(14) Incremental Cost-Effectiveness Ratio (ICER)

[Definition]

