**10.5.3　Secondary Outcome Analysis**

(1) Operative time

(2) Estimated blood loss

For FAS, calculate summary statistics (sample size, mean, standard deviation, minimum, median, maximum) by group. Perform Student's t-test for between-group comparisons and calculate p-values.

(3) Proportion achieving the minimal clinically important difference (MCID) in cervical JOA score recovery rate at postoperative 1 and 2 years

For the FAS, calculate the proportion achieving the MCID (JOA score recovery rate of 52.8%) for the cervical JOA score recovery rate at postoperative 1 year and 2 years by group. For between-group comparisons, calculate the difference in the proportion achieving the MCID (52.8% recovery rate) and its 95% confidence interval, then perform Fisher's exact test. Use the Clopper-Pearson method to calculate the confidence interval.

(4) Health-related QOL (EQ-5D) at postoperative 1 and 2 years

(5) Severity of neck pain, upper limb pain, and upper limb numbness (VAS) at postoperative 1 and 2 years

(6) Neck disability index (NDI) at postoperative 1 and 2 years compared to preoperative

For FAS, perform analyses similar to those for primary endpoints on the change in each assessment item from preoperative to 1 year postoperatively.

Additionally, perform analyses similar to those for secondary endpoint (2) on the change in each assessment item from preoperative to 1 year and 2 years postoperatively.

(7) Retention rate of enlarged lamina at postoperative 1 and 2 years (Retention rate)

For FAS, the change in the retention rate of enlarged lamina from preoperatively to 1 year postoperatively will be analyzed similarly to the primary endpoint.

Furthermore, the change in the retention rate of enlarged lamina from preoperatively to 1 and 2 years postoperatively will be analyzed similarly to secondary endpoint (2).

(8) Percentage of hinge fractures at postoperative 1 and 2 years

(9) Percentage of bone union of gutter at postoperative 1 and 2 years

For FAS, calculate the percentage for each evaluation item at 1 year and 2 years postoperatively by group. For between-group comparisons, calculate the difference in the percentage for each evaluation item and its 95% confidence interval, and perform Fisher's exact test. Use the Clopper-Pearson method to calculate the confidence interval.

　(10) Sagittal alignment of cervical spine at postoperative 1 and 2 years (C-SVA, C2-7 angle, T1 slope)

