For FAS subjects, perform analyses similar to those for primary endpoints on the change in each evaluation item from preoperatively to 1 year postoperatively.

Additionally, perform analyses similar to those for secondary endpoint (2) on the change in each evaluation item from preoperatively to 1 and 2 years postoperatively.

(11) Paraspinal muscle cross-sectional area (C4/5 level) at postoperative 1 and 2 years

For FAS, perform the same analysis as for primary endpoints on the change in paraspinal muscle cross-sectional area from preoperatively to 1 year postoperatively.

Additionally, perform the same analysis as for secondary endpoint (2) on the change in paraspinal muscle cross-sectional area from preoperatively to 1 and 2 years postoperatively.

(12) Dural sac cross-sectional area (C3/4, C4/5, C5/6, C6/7 levels) at postoperative 1 and 2 years

For FAS subjects, perform the same analysis as for the primary endpoint on the change in dural canal area from preoperative to 1-year and 2-year postoperative time points.

Additionally, perform the same analysis as for secondary endpoint (2) on the change in dural canal area from preoperative to 1-year and 2-year postoperative time points.

(13) Grading of the mass posterior to the dural sac at postoperative 1 and 2 years

For FAS subjects, classify posterior spinal canal compression at 1 and 2 years postoperatively into mild (Grade 1-3) and severe (Grade 4-5). Calculate the proportion of severe posterior spinal canal compression at 1 and 2 years postoperatively by group. For between-group comparisons, calculate the difference in the proportion for each evaluation item and its 95% confidence interval, then perform Fisher's exact test. Use the Clopper-Pearson method to calculate the confidence interval.

(14) Incremental Cost-Effectiveness Ratio (ICER)

Calculate the ICER of the test treatment group relative to the control group.

Refer to Section 8.1.2 for details on the calculation method.

(15) Surgical complication incidence

For SAS, calculate the number of cases and rates of each complication by the following categories for each assigned group.

・Intraoperative complication rate (from start of surgery to end of surgery (wound closure))

・Early postoperative complication rate (from end of surgery (wound closure) to within 30 days postoperatively)

・Late postoperative complication rate (from postoperative day 31 to within 2 years postoperatively)

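### Section 10.5.3 analyses retention rate as a change from a preoperative value that does not exist, and refers the 1- and 2-year change analyses of several secondary endpoints to the blood-loss t-test

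*Protocol*

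**What the plan says.** **Retention rate, definition.** Protocol 8.2, item (7): "The retention rate is calculated for each enlarged lamina identified on CT scans at postoperative 1 and 2 years". A mean per patient is also calculated. The CT row of the schedule in 7.2.1 is labelled "Postoperative: Enlarged Laminar Retention Rate, Hinge Fracture/Bone Union".

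**Retention rate, analysis.** Protocol 10.5.3, item (7), gives two analyses. In the first, "the change in the retention rate of enlarged lamina from preoperatively to 1 year postoperatively will be analyzed similarly to the primary endpoint". In the second, the "change in the retention rate of enlarged lamina from preoperatively to 1 and 2 years postoperatively will be analyzed similarly to secondary endpoint (2".

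**The reference.** In 10.5.3 the endpoint with that number is "2) Estimated blood loss". Its method, shared with operative time, begins: "For FAS, calculate summary statistics (sample size, mean, standard deviation, minimum, median, maximum) by group". Student's t-test follows, with p-values as the only comparative output named.

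**Other items sent there.** For EQ-5D, VAS and NDI, items (4)-(6), the instruction is to "perform analyses similar to those for secondary endpoint (2) on the change in each assessment item from preoperative to 1 year and 2 years". Sagittal alignment, item (10), is told to "perform analyses similar to those for secondary endpoint (2) on the change in each evaluation item". Items (11) and (12), muscle area and dural sac area, carry the same reference.

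**The repeated-measures analysis that exists.** Section 10.5.2 describes an MMRM of the JOA recovery rate at 1 and 2 years, as a secondary analysis of the primary endpoint. Its fixed effects include preoperative JOA score, age, sex and diagnosis.

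**The concern.** A retention rate describes how much of the surgical opening is kept. No lamina is open before surgery, so a change from the preoperative state has no starting value. Section 5.1 chose this endpoint as the objective indicator of reclosure for the safety assessment, so its analysis should be executable as written.

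The reference to blood loss is a separate matter. Blood loss is measured once, has no baseline and needs no repeated-measures model. A change measured at 1 and 2 years has all the features that a simple t-test ignores. At stake are the 2-year patient-reported and imaging comparisons, which as written have no baseline adjustment, no required interval, and no use of 1-year data from patients missing at 2 years. Section 10.2 expects about 20% dropout, and 10.4 rules out imputation.

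**Working it through.** **1. Plan's own figure.** Inputs from 10.2: SD 40, margin 20, one-sided alpha 0.025, power 0.9, true difference taken as 0. The normal formula gives 2 × (1.960 + 1.282)² × 40² / 20² = 84.1, so 85 per arm. With the noncentral t, 85 per arm gives power 0.8999 and 86 gives 0.9032, hence 172. Then 86 / 0.8 = 107.5, so 108 per arm and 216 in total. The stated figures reproduce, and none depends on the secondary analyses.

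**2. Is there a preoperative retention rate?**
- 8.2 (7) calculates it per enlarged lamina at 1 and 2 years.
- 7.2.1 marks CT preoperatively and at 1 week, 1 year and 2 years, but labels the rate a postoperative reading.
- 7.2.2 lists no such value among the background items. Its CT row names the rate without a time point, so it supplies no baseline either.

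Suppose a constant c (0 or 100%) stood in for the missing value. The group difference in change is (mean post, suture-anchor − c) − (mean post, plate − c), which is the group difference in postoperative means. As a covariate, c would be collinear with the intercept: intercept, group and c give a design of rank 2, not 3. The change adds nothing, and the analysable quantity is the postoperative value.

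**3. What each item gets, read literally.**

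| Item | 1 year | 2 years |
|---|---|---|
| (4)-(6), (10), (11) | primary-type ANCOVA and t-test | t-test only |
| (7) | neither can be run | cannot be run |
| (12) | primary-type ANCOVA and t-test | primary-type ANCOVA and t-test |

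Where both methods apply to the same change, nothing says which governs.

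**4. Size of the efficiency loss.** Let s be a common SD before and after surgery and rho the correlation between the two measurements.
- Variance of an unadjusted change score: 2s²(1 − rho)
- Residual variance after adjusting for the outcome's own baseline: s²(1 − rho²)
- Ratio, adjusted to unadjusted: (1 + rho)/2
- Reduction forgone: (1 − rho)/2
- Interval width, unadjusted to adjusted: the square root of 2/(1 + rho)

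| rho (assumed) | Variance ratio | Reduction forgone | Interval width ratio |
|---|---|---|---|
| 0.3 | 0.65 | 35% | 1.24 |
| 0.5 | 0.75 | 25% | 1.155 |
| 0.7 | 0.85 | 15% | 1.085 |
| 0.9 | 0.95 | 5% | 1.026 |

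This applies to the 2-year change in (4)-(6), (10) and (11).

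**The case against.** The case for leaving this to the statistical analysis plan has some weight. Section 10 calls itself an overview and lets that plan alter methods. Section 10.7 puts the primary analysis of the efficacy endpoints at 1 year, when every affected item except (7) already has an ANCOVA-type analysis. The endpoint lists consistently describe retention rate at 1 and 2 years, so the quantity of interest is clear despite the stray reference to a preoperative value. The reference to blood loss looks like a slip for the MMRM, and if that model is run the loss from the t-test does not arise.

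These arguments limit the severity but do not remove the point. The protocol does not leave these matters open: it states a change that cannot be formed and names a method that does not fit. That the MMRM was intended is an inference; the protocol does not say so.

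The objection on covariates largely stands. A similar analysis need not carry preoperative JOA over to EQ-5D or NDI, and covariate detail commonly belongs in the analysis plan. It is therefore not a separate error here. It needs stating only because the gain in the table depends on own-baseline adjustment; restoring the MMRM with preoperative JOA as its only baseline score would not by itself deliver it.

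A reader might convert the loss into patients: 20% to 35% of 86 is about 17 to 30 per arm, for rho of 0.6 to 0.3. The documents do not support that as the cost of the wrong reference. No correlation is given, higher values shrink the figure towards zero, and it presupposes the own-baseline covariate.

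**Conclusion.** The point holds as a should-fix for secondary endpoints. Item (7) cannot be analysed as written. The 2-year change in (4)-(6), (10) and (11) rests on an unadjusted t-test in patients with 2-year data, with no interval required. Item (12) keeps a primary-type analysis at 2 years.

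The variance reduction forgone is 35% to 5% for rho from 0.3 to 0.9. That range assumes equal SDs before and after surgery, a comparison with own-baseline adjustment, and a correlation that the documents do not report.

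Two stronger conclusions are tempting. One is that the comparisons fail or are biased. The t-test on change is valid under randomisation, so choosing it loses efficiency without adding bias; only item (7) is inexecutable, and its postoperative values remain analysable. The other is that retention rate must be expressed relative to the 1-week CT. Section 8.2 names only 1 and 2 years, and the formula is in Figure 4, which is not shown, so the role of the 1-week scan cannot be settled from the text.

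**What to change.** In 10.5.3:

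- **Item (7):** analyse the patient-mean retention rate at 1 and 2 years itself, with no preoperative value as baseline or covariate. Use the 1-week CT as reference or covariate only if that agrees with the Figure 4 formula.
- **Items (4)-(7) and (10)-(12):** replace the reference to secondary endpoint 2 with an explicit reference to the MMRM of 10.5.2, after confirming that this was the intention, and report differences with 95% confidence intervals.
- **Items (4)-(6) and (10)-(12):** state that each model adjusts for the preoperative value of the outcome being analysed. Item (7) must be left out of this sentence, or the non-existent baseline returns.

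The cost is wording in the protocol, carried into the statistical analysis plan. The preoperative measurements and all CT scans, including the one at 1 week, are already scheduled. Sample size and the primary analysis do not change. Because the trial is open-label, the edit is best made before outcome data accrue.

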## **3.3 Rationale for Study Design**

Therefore, this randomized non-inferiority trial aims to demonstrate that the conventional, less expensive suture anchor method is non-inferior in efficacy and safety to the plate method, which is becoming one of the current standard procedures.

The primary endpoint, representing the most relevant measure of efficacy for this surgery, is the JOA score. The pre- and post-operative recovery rate in the JOA score^4)^ is commonly used as an indicator of therapeutic effect in surgical treatment. Therefore, the primary endpoint is defined as the recovery rate in the cervical JOA score between pre- and post-operative measurements. The cervical JOA score is the most widely used international indicator for evaluating treatment outcomes in compressive myelopathy.

Cervical JOA Score Recovery Rate = (Postoperative Score - Preoperative Score) / (17 - Preoperative Score) × 100 (%)

*JOA: Japanese Orthopaedic Association

The primary analysis time point was set at 1 year postoperatively, based on the rationale that recovery rates do not change significantly beyond 1 year postoperatively¹⁴⁾. Results at 2 years postoperatively were also evaluated as a final analysis.

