# **４．****Objectives of the Clinical Study**

To verify, through a randomized controlled trial, that the conventional, low-cost suture-anchor method does not show inferior efficacy or safety compared to the mini-plate method—a double-door laminectomy using plates, which is becoming one of the current standard procedures—in patients with DCM requiring cervical laminoplasty.

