(4) ～(6)　The JOA score is a physician-led assessment of spinal cord symptoms originating from the cervical spine. Patient-reported outcomes such as EQ-5D, VAS, and NDI were set as secondary endpoints. Furthermore, EQ-5D will also be used as the utility value when calculating the incremental cost-effectiveness ratio.

(7) For safety assessment, the retention rate^7)^ (Figure 4), an objective indicator for enlarged lamina reclosure, was set as a secondary endpoint.

[figure not shown]

(8) As a safety endpoint, the proportion of hinge fractures in enlarged laminar segments on CT^8)^ was set as a secondary endpoint.

(9) As an endpoint for surgical goal achievement, the proportion of hinge fractures showing bone union on CT was set as a secondary endpoint.

(10) Postoperative cervical kyphotic deformity is a morphological change that leads to recurrence of spinal cord symptoms and poor outcomes in cervical laminoplasty^7-9)^. As indicators of kyphotic deformity, the C2-7 lordotic angle and C-SVA were set as secondary endpoints, along with the C7 slope as a factor influencing these (Figure 5).

[figure not shown]

(11) Reduction in the cross-sectional area of the paraspinal muscles (Fig. 6), which are cervical extensors, has been reported as a factor influencing occipital pain^20)^ and as a factor involved in post-laminoplasty reclosure^7)^. Therefore, the postoperative paraspinal muscle area at the C4-5 level was set as a secondary endpoint.

[figure not shown]

(12)(13) Post-laminectomy membrane, caused by posterior dural scarring after laminectomy, is considered a factor in spinal cord re-compression^21)^. However, its incidence rate across different laminoplasty techniques remains unclear. Postoperative dural canal area and the Grading of the mass posterior to the dural sac ^22)^ (Figure 7) were set as secondary endpoints to evaluate spinal cord re-compression.

[figure not shown]

(14) A key objective of this study is to demonstrate that the experimental treatment (suture- anchor) is non-inferior in efficacy and safety to the control treatment (mini-plate), while being less expensive and offering superior cost-effectiveness. As an indicator for comparing the cost-effectiveness between the experimental and control groups, the commonly used measure, ICER, was set as a secondary endpoint.

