**10.5.2　Analysis of Primary Endpoints**

・Recovery Rate in Cervical JOA Score Before and After Surgery

For FAS participants, calculate the least squares mean and its 95% confidence interval for the cervical JOA score recovery rate at 1 year post-surgery using analysis of covariance. Also calculate the between-group difference in least squares means (suture anchor method vs. plate method), its 95% confidence interval, and the p-value. The analysis model included the following covariates: group, preoperative JOA score, age (≤64 years, 65–74 years, ≥75 years), sex, and preoperative diagnosis (cervical spondylotic myelopathy (CSM), ossification of the posterior longitudinal ligament (OPLL)).

The suture-anchor method will be considered non-inferior to the mini-plate method if the lower limit of the 95% confidence interval for the least squares mean difference between groups at 1 year postoperatively exceeds –20%. Additionally, as a secondary analysis, a Mixed-effects Model for Repeated Measures (MMRM) analysis will be performed using the first available subject (FAS) population, with the recovery rate in cervical JOA scores at 1 year and 2 years postoperatively relative to preoperatively as the response variable. The analysis model will include the following as fixed effects: group, time point, group-time interaction, preoperative JOA score, age (≤64 years, 65–74 years, ≥75 years), sex, and preoperative diagnosis (CSM, OPLL). Using this model, the least squares mean and 95% confidence interval for the recovery rate in cervical JOA scores before and after surgery at 1 year and 2 years postoperatively will be calculated. Additionally, the between-group differences in the recovery rate of cervical JOA scores before and after surgery at 1 year and 2 years postoperatively, along with their 95% confidence intervals and p-values, were calculated.

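### Non-inferior safety is a stated aim of the trial, but no safety endpoint has a margin or decision criterion, and the Fisher test planned for hinge fractures cannot supply one

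*Protocol*

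**What the plan says.** **The aim.** Section 4 sets out to verify that the suture-anchor method "does not show inferior efficacy or safety compared to the mini-plate method". Section 3.3 says the trial is to demonstrate that it "is non-inferior in efficacy and safety to the plate method", and the rationale for endpoint (14) in section 5.1 says that it "is non-inferior in efficacy and safety to the control treatment". Sections 1 and 3.4 say the same in substance. Sections 1 and 5.2.1 class the study as verification research.

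**The safety endpoints.** Section 5.1 gives retention rate (7) a safety purpose. For (8) it reads: "As a safety endpoint, the proportion of hinge fractures in enlarged laminar segments on CT". Surgical complications, including reoperation, are endpoint (15).

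**The rule.** Section 10.5.2 states: "The suture-anchor method will be considered non-inferior to the mini-plate method if the lower limit of the 95% confidence interval". In full, the condition is that "the lower limit of the 95% confidence interval for the least squares mean difference between groups at 1 year postoperatively exceeds –20" percent. It concerns the JOA recovery rate only.

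**The safety analyses (section 10.5.3).**
- Retention rate: modelled in the same way as the primary endpoint, with no margin in its own units.
- Hinge fracture: percentages by group, then "calculate the difference in the percentage for each evaluation item and its 95% confidence interval, and perform Fisher's exact test", and "Use the Clopper-Pearson method to calculate the confidence interval".
- Complications: counts and rates by assigned group, with no comparison.

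**The concern.** A non-inferiority conclusion needs a stated amount of harm that the data must exclude. For safety, the protocol announces the conclusion and never states the amount. For hinge fracture the only test has equality as its null hypothesis, whereas the objective needs a null under which anchors are worse by an unacceptable amount. Failing to reject equality may mean that the arms are alike, or only that the sample is small, and the sample was sized for the JOA score alone.

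Section 3.4 expects the results to inform the choice between a cheaper and a dearer technique. A statement that safety was shown to be non-inferior would bear directly on that choice, and nothing in the planned analysis could support it.

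**Working it through.** **1. Sample size available (section 10.2).** Inputs: margin 20, SD 40, true difference 0, one-sided 0.025, power 0.90.

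n per arm = 2 × 40² × (1.960 + 1.282)² / 20² = 8 × 10.51 = 84.1, so 85 (170 in total). With the t distribution it is 86 per arm (power 0.903), which reproduces the stated 172. Then 172 / 0.8 = 215, or 216 in equal arms. Fracture data would thus come from about 86 evaluable to 108 enrolled patients per arm. No safety quantity enters this calculation.

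**2. What Fisher's test would miss.** Three inputs are assumptions: the plate-arm fracture rate (not given), one yes/no result per patient (section 8.2 assesses each lamina and fixes no denominator), and a two-sided 0.05 level (not stated for this test). Exact power is the sum, over all pairs of counts with Fisher p ≤ 0.05, of the product of the two binomial probabilities. The miss rate is 1 minus power.

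| Plate v anchor | Power, 86 / 108 per arm | Doubling missed |
|---|---|---|
| 5% v 10% | 0.160 / 0.209 | 84% / 79% |
| 10% v 20% | 0.377 / 0.470 | 62% / 53% |
| 15% v 30% | 0.590 / 0.706 | 41% / 29% |
| 20% v 40% | 0.782 / 0.871 | 22% / 13% |

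Power for a doubling reaches 50% at a plate-arm rate of about 12.9% (86 per arm) or 10.6% (108 per arm), and 80% at about 20.6% or 17.6%.

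**3. Observed results that stay non-significant.** 5/108 (4.6%) v 14/108 (13.0%) gives p = 0.052. 9/86 (10.5%) v 19/86 (22.1%) gives p = 0.062.

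**4. What an interval would say.** With identical observed counts, the Newcombe (Wilson-based) upper 95% limit for the difference is 7.3 points at 4/86, 9.6 at 9/86, 6.3 at 5/108 and 8.4 at 11/108. Even a perfect tie leaves an excess of roughly 6 to 10 points unexcluded at these rates.

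**5. Effect of the denominator.** Assume 3 laminae per patient and 86 patients per arm, using a normal approximation. At 5% v 10%, 258 laminae per arm treated as independent give 58% power. With an assumed intracluster correlation of 0.3, the effective number is 258 / (1 + 2 × 0.3) = 161 and power is 40%. The open denominator therefore changes the answer materially.

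**6. What a margin would require.** n per arm = 2p(1 - p) × 10.51 / margin², for equal true rates p, one-sided 0.025 and power 0.90. The margins are illustrative, not proposals.
- 10 points: 100 per arm at 5%, 190 at 10%, 337 at 20%.
- 15 points: 85 per arm at 10%, 150 at 20%.

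With 86 per arm and 10 points, power is about 85% at a 5% rate, 59% at 10% and 37% at 20%.

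**The case against.** **The protocol never says that p > 0.05 means safe.** This stands. A reader might infer that a non-significant Fisher result will be taken as verified safety, or that Fisher's test is the decision rule for fractures. The text supports neither: section 10.5.3 also plans the difference and its interval, and it ties no result to a safety conclusion. The defect is a missing criterion, not a wrong one. It also follows that missing CT scans cannot be said to make the claim easier to reach, because no rule for reaching it exists.

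**A doubling would not necessarily be missed.** This also stands. A reader might infer that a doubling would usually go undetected. That depends on a rate the protocol does not give, and at 15% or more per patient a doubling is usually detected.

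**Safety does not rest on Fisher's test alone.** Correct. Retention rate gets an adjusted mean difference with an interval, and complications are tabulated. Neither fills the gap. The -20 point limit is derived in section 10.2 and applied in section 10.5.2 for JOA recovery, and nothing carries it over to retention rate. A table of rates has no criterion.

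**The interval is already planned, and details may go to the SAP.** Partly correct. However, no limit of the interval is linked to a conclusion, and Clopper-Pearson is a method for one proportion, not for a difference between two. The mismatch lies between the protocol's own objective and its own analysis section, and the objective's wording is set in the protocol.

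**Conclusion.** The point holds in this form: the protocol promises a non-inferiority conclusion on safety and gives no safety endpoint a margin or criterion by which to reach it. That follows from the text and needs no assumed rate.

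The size of the problem for hinge fracture is conditional. With one result per patient and a two-sided 0.05 level, Fisher's test misses a doubling in 53 to 84% of trials at plate-arm rates of 5 to 10%, and in 13 to 41% at 15 to 20%. The crossover is at about 11 to 13%. Whatever the rate, a non-significant result from this test would not be evidence of non-inferior safety.

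The primary JOA comparison is not affected.

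**What to change.** **Preferred.** In sections 1, 3.3, 3.4, 4 and 5.1 (14), limit the non-inferiority claim to JOA recovery and describe safety as estimated. In section 10.5.3 (8):
- fix the denominator (patient, or lamina with allowance for clustering);
- base the safety statement on the 95% confidence interval of the risk difference, suture-anchor minus plate, by a valid two-sample method such as Newcombe's;
- report the upper limit as the largest excess that the data do not exclude;
- state that p > 0.05 is not evidence of non-inferior safety.

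**Alternative.** If the sponsor keeps the claim of non-inferior safety, it should name one safety endpoint, fix and justify its own margin before data lock, and state the power at the planned sample size. Step 6 of the working shows that this power could be low if the fracture rate is 10% or more.

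**Cost.** The preferred change is wording in the objectives and one analysis item, with no extra patients, visits or image readings. The price is a weaker safety claim than the protocol now promises. The alternative may need more patients, depending on the margin and the rate.
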